### Allocation and blinding

A random number table generated by SPSS 20.0 software (IBM Co., Armonk, NY, USA), using the randomization method, will be employed to assign the participants to each group at a ratio of 1:1:1. Patients will be enrolled during allocation according to the sequence of ICU admission. For masking, random sequences and group assignments will be sealed in opaque envelopes. As this study is a comparative assessment of treatment modalities, blinding will not be feasible. Masking related to the participant treatment arm allocation and to the treatment team for the baseline and follow-up assessments will be applied for the assessment team, data manager, and statistician.

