### Participants

Three separate cohorts of patients admitted to the ICU of Guangdong Hospital of Chinese Medicine who satisfy the inclusion/exclusion criteria outlined below will be recruited for this study. Before recruitment, the research team will prepare and publish recruitment advertisements and hold consultation meetings with doctors specializing in critical care in the hospital.

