### Data collection and management

The Second Affiliated Hospital of Guangzhou University of Chinese Medicine will be in charge of the data management and statistical analysis in this study. The clinical observations do not participate in statistical analysis. The study personnel will undergo training sessions on data collection and will be individually tested regarding data entry as well as outcome assessments before initiation of the trial. The study data will be collected and managed using SPSS 20.0. A follow-up visit or telephone follow-up will be conducted at 28 days and 12 weeks after the intervention.

An independent data safety monitoring board (DSMB) will receive the trial data from the biostatistician and choose to either continue the study as planned, change the study protocol, or stop the trial early due to harm.

The participants’ medical records will be maintained at the hospital, and the investigator, research authority, and ethics committee will be allowed access to this information. Any public report on the results of this study will not disclose the participants’ personal identities. Every effort will be made to protect the privacy of the participants’ personal medical data, according to law. Personal and medical information will be kept confidential in a safe and reliable location. At any time, the participants will be able to request access to their personal information (such as their address and contact information) and modify it if necessary.

The clinical specimen department of Guangdong Academy of Chinese Medicine will carry out the unified management and preservation of collected blood specimens. Motilin levels will be determined by ELISA at the Laboratory of Critical Care Medicine of Guangdong Academy of Chinese Medicine.

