### Statistical analysis

All statistical analyses will be performed using SPSS 20.0 software. Measurement data will be expressed as the mean ± standard deviation. Normality tests and homogeneity tests of variance will also be performed. In cases of normal distribution and homogeneity of variance, a *t* test will be conducted; otherwise, a non-parametric test will be employed. If the measurement data conform to a normal distribution, an independent sample *t* test will be applied between two groups; one-way analysis of variance (ANOVA) will be utilized between the three groups. In the case of non-normal distribution, two groups will be compared using the Mann–Whitney *U* test, and the three groups will be compared with the Kruskal–Wallis test. Enumeration data between two and three groups will be compared using chi-square/Crosstab statistical analysis, and the results will be expressed as the frequency constituent ratio (%). *P* < 0.05 will indicate statistical significance.

For patients who die or are lost to follow-up, their observation time will be censored at the time of death or date of last contact. For patients with early withdrawal who are lost to follow-up, intention-to-treat analysis (ITT) will be applied. For the second endpoint (6), cumulative proportion survival curves according to Kaplan–Meier analysis will be obtained for each group and compared with the log-rank test. To explore the group effect on the time to the event of composite outcome, with adjustment for baseline covariates, the Cox regression model will be used.

The trial will be prematurely paused or closed by the DSMB to evaluate safety information from the study or if there is evidence of harm in the study. The principal investigator (PI) will be able to access these interim results.

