### Oversight and monitoring

The coordinating center, steering committee, and endpoint adjudication committee’s responsibilities will be assumed by the ethics committee of Guangdong Hospital of Chinese Medicine, with review of the data for at least half a year.

Monitoring will be performed by an independent DSMB consisting of three members with expertise in critical care medicine, clinical trial methodology, and biostatistics. The DSMB will receive the trial data from the biostatistician and choose to either continue the study as planned, change the study protocol, or stop the trial early due to harm. The DSMB will submit the experimental data to the ethics committee of Guangdong Hospital of Traditional Chinese Medicine for review at least once every 6 months. Related data from each DSMB meeting will be retained in a secured file for inspection by regulatory authorities.

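### The PI has unrestricted access to interim results, and accumulating data go to the committee that also steers the trial and adjudicates endpoints, with no stated firewall

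*Protocol article*

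**What the plan says.** All references are to the protocol article.

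- **Statistical analysis.** The DSMB's role is described first: "The trial will be prematurely paused or closed by the DSMB to evaluate safety information from the study or if there is evidence of harm". The next sentence reads "The principal investigator (PI) will be able to access these interim results". It is not limited to pooled data, to a recommendation or to a harm signal.
- **Oversight and monitoring.** Several roles are given to one body: "The coordinating center, steering committee, and endpoint adjudication committee’s responsibilities will be assumed by the ethics committee of Guangdong Hospital of Chinese Medicine". In the same section, "The DSMB will submit the experimental data to the ethics committee", at least once every six months.
- **Data collection and management**, repeated under Oversight and monitoring. The DSMB may "choose to either continue the study as planned, change the study protocol, or stop the trial early due to harm". Stopping is tied to harm; changing the protocol is not tied to any ground.
- **Allocation and blinding.** "As this study is a comparative assessment of treatment modalities, blinding will not be feasible". Masking "will be applied for the assessment team, data manager, and statistician".
- **Participants.** Patients are those "admitted to the ICU of Guangdong Hospital of Chinese Medicine", so there is one site.

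**The concern.** Interim comparisons are normally kept from those who run a trial, because knowing the trend can change how later patients are selected, retained and judged. Here two routes out of the DSMB are written into the plan. One leads to the PI of a single open-label ICU. The other leads to a committee that receives the accumulating data while also holding the steering and adjudication roles.

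Three kinds of decision are at stake: who is judged eligible, who is taken out of the study for intolerance, and whether a pneumonia is counted. These are affirmative rules in the article, not details left to an unseen analysis plan or DSMB charter, so they can fairly be reviewed as written.

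**Working it through.** No figure in the plan is in dispute. The check sets the sections side by side, with one small calculation for scale.

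**1. What the interim results are.** The sentence granting PI access follows one about safety information and evidence of harm. The article describes no interim efficacy comparison. It does not say whether results are by arm, coded or pooled, and it states no restriction. In an open-label single ICU, a PI holding detailed interim data could in any case link much of it to arms.

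**2. Who is masked.** Allocation and blinding lists the assessment team, the data manager and the statistician. It lists neither the PI nor the ethics committee. PI access therefore does not contradict that section, and that section gives no protection against it.

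**3. Whether the recipient and the adjudicator are the same body.** Oversight and monitoring names the ethics committee twice, with hospital names that differ by one word (Traditional). They read as one hospital. If they were two bodies, the adjudication part would fall and the PI part would stand.

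**4. Where influence could act.**

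| Decision | Section | Room for judgement |
|---|---|---|
| Suitability for enteral nutrition; ICU stay expected to exceed 48 h | Inclusion criteria | Yes, but allocation is concealed in sealed opaque envelopes |
| Drop-out for non-tolerance with complications | Criteria for drop-out | Yes; no numeric threshold |
| Pneumonia: new or changed infiltrate, purulent secretions | Secondary outcome | Yes, within listed criteria |
| Feeding intolerance during treatment | Interventions; Table 1 | Little: residual volume above 250 mL or above 500 mL |
| Caloric goal | Primary outcome | Little: 25 kcal/kg of ideal body weight, set by one nutritionist |

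The first three rows are the plausible routes. Drop-out matters most for the primary outcome, which covers only the first 5 days.

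**5. Frequency of transfer.** Trial status gives recruitment from July 2020 to December 2023.

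- Months: 6 (July to December 2020) + 3 × 12 (2021 to 2023) = 42.
- Transfers at the minimum frequency: 42 / 6 = 7, the seventh at about the end of recruitment.
- Patients between transfers, assuming even accrual of 90: 90 / 7 ≈ 13.

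Six months is the longest permitted interval, so about 7 is a minimum. The count applies to the ethics committee only. No frequency is given for PI access.

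**The case against.** The strongest case on the other side is that little is actually disclosed. The passage is about safety. The DSMB's data come from the biostatistician, and the statistician is masked, so the output may already be coded or pooled. A charter that is not shown may settle this. The clinical team in an open-label ICU sees arms and outcomes anyway. Sealed envelopes mean that knowing a trend does not reveal the next allocation. Under Protocol amendments, changes need ethics approval through a process independent of the investigators and sponsor. Ethics review of safety data is ordinary practice.

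Much of this stands, and it rules out several stronger readings that a reader might infer:

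- **That the PI will learn which arm is ahead.** The article does not say the results are by arm or concern efficacy.
- **That the plan contradicts its own masking.** The PI and the ethics committee were never listed as masked.
- **That there are about 7 disclosures to the PI.** The six-monthly transfers go to the ethics committee.
- **That intolerance calls during feeding are discretionary.** They are defined by residual volume.
- **That sending data to an ethics committee in itself undermines the DSMB.** The difficulty is only that this committee also adjudicates and steers.

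The objection does not remove the core. PI access is granted without limit. Envelopes conceal allocation but do not govern drop-out or adjudication. The amendment safeguard relies on the same committee that receives the data. Seeing one's own patients day by day is also not the same as seeing an accumulated comparison.

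**Conclusion.** The point holds as a risk of bias created by stated rules on access. It is not an internal contradiction and not a documented event. Two things are fixed badly: unrestricted PI access to interim results, and transfer of accumulating data to a committee with steering and adjudication duties, with no stated firewall. The decisions exposed are judgement-based eligibility (weakly, given concealment), drop-out for non-tolerance, and pneumonia adjudication.

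The size of any bias cannot be estimated from the article. The only figure available is the minimum of about 7 transfers to the committee over about 42 months. The conclusion assumes that the two hospital names denote one institution and that no unseen charter already restricts access. The change is worth making because it is cheap, not because harm has been shown.

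**What to change.** In Statistical analysis, replace the sentence on PI access with:

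> Interim results by arm are seen only by the DSMB; the masked statistician prepares reports with coded arms and the DSMB holds the code. The PI receives only the DSMB recommendation and pooled data; individual serious adverse events are reported as usual.

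Coding the arms is needed: a statistician who prepared openly labelled reports would no longer be masked, and the article names no second statistician.

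In Oversight and monitoring, add:

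> Anyone who adjudicates endpoints or acts in the steering role does not see interim data by arm. The DSMB may recommend protocol changes on safety grounds; these are approved as described under Protocol amendments.

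Align the parallel sentence in Data collection and management on the DSMB's options.

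**Cost.** A few sentences and no new data. The PI loses sight of interim comparisons, the reports must be coded, and the ethics committee must either keep its adjudicating and steering members away from by-arm data or receive pooled data. Enrolment was already under way when the article was written, so the change protects only decisions still to be made.

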### Oversight and monitoring

The coordinating center, steering committee, and endpoint adjudication committee’s responsibilities will be assumed by the ethics committee of Guangdong Hospital of Chinese Medicine, with review of the data for at least half a year.

Monitoring will be performed by an independent DSMB consisting of three members with expertise in critical care medicine, clinical trial methodology, and biostatistics. The DSMB will receive the trial data from the biostatistician and choose to either continue the study as planned, change the study protocol, or stop the trial early due to harm. The DSMB will submit the experimental data to the ethics committee of Guangdong Hospital of Traditional Chinese Medicine for review at least once every 6 months. Related data from each DSMB meeting will be retained in a secured file for inspection by regulatory authorities.

### Adverse events and injury

Although adverse events (AEs) of the intervention measures in this study will be rare, any AEs that occur in subjects during clinical observation might be related to the drug of interest. The AE report form will be completed during the trial. The time of occurrence, severity, duration, actions taken, and outcomes of AEs will be recorded, and those occurring during follow-up will be reported to the sponsor in a timely manner. Furthermore, serious AEs will be reported simultaneously to the adverse drug reaction (ADR) monitoring center of the local authority within 24 h and the sponsor. The study team will prioritize unpaid examination and treatment according to the regulations of the ethics committee. Auditing trial conduct will occur once a year.

### Protocol amendments

The process will be independent from the investigators and the sponsor. If the research plan needs to be modified, the ethics committee will be provided with relevant explanatory materials and an application, and the modification will only be carried out after approval.

## Discussion

Although guidelines state that EN should be given by a pump or gravity drip, there is no agreement on whether continuous pumping should be applied or on the duration of pumping. The DFM-GFC study will explore the impact of three common EN delivery methods (continuous, intermittent, cyclic) on heat entrapment, gastrointestinal complications, and the occurrence of aspiration and aspiration pneumonia. In addition, costs associated with EN delivery (equipment use and complications) will be compared. Although the incidence of complications will not decline significantly, the cost of treatment will be lower if the intermittent pumping and cyclic pumping feeding method are accomplished in less time than the continuous pumping feeding method.

Current guidelines often compare continuous feeding to intermittent feeding (done either via manually set gravity rate or volumetric pump) [1]. The number of volumetric pumps available may vary from institution to institution. However, the use of a volumetric pump in place of manual infusion (gravity drip) for intermittent feedings allows for more consistent feeding. All three feeding methods, continuous, intermittent, and cyclic are commonly used in hospitals [14, 15]. Nonetheless, with the application of a volumetric pump, manual injection is no longer used for intermittent feeding, and the time of each injection can also be extended to several hours. Continuous feeding, intermittent feeding, and cyclic feeding have become three common feeding methods. Some studies [13, 16, 17] have demonstrated that continuous pumping does not improve blood sugar levels, stomach retention, or the occurrence of ventilator-associated pneumonia.

According to an individual’s physiology and habits, it is necessary to rest during the inter-meal time, the physiologically appropriate number of meals per day for humans is an enigma. According to Homer, only two, rather than three, meals were eaten per day in ancient Greece. During sleep, peristalsis of the gastrointestinal tract is slowed, and secretion of digestive juices is reduced. Some studies [18] have demonstrated that there is no difference in the amount of water in the small intestine and the amount of hormones secreted by the small intestine using continuous pumping and bolus through a gastric tube in healthy individuals. Therefore, is intermittent eating the result of physical conditions and social behavior or the physiological needs of organs?

A previous study [19] has found that intermittent bolus feeding enhances muscle protein synthesis to a greater extent than continuous feeding by eliciting a pulsatile pattern of amino acid- and insulin-induced translation initiation. Moreover, it increases difficulty in moving or turning [20]. Overall, continuous pumping is not a physiological condition. Although intermittent feeding can be cost-effective for patients, it is unclear whether continuous pumping is optimal in terms of treatment effectiveness and complications. Therefore, this study will compare the effects of continuous feeding, cyclic feeding, and intermittent feeding in critically ill patients, including complications such as vomiting, diarrhea, length of stay in the ICU and increased hospitalization costs due to aspiration pneumonia. In summary, this study will reveal cyclic feeding or intermittent feeding is the optimal treatment for EN in critically ill patients and will serve as a basis for the development of EN guidelines.

## Trial status

The systematic reviews of quantitative and qualitative literature have been completed and published. Enrolment is ongoing. Recruitment started in July 2020 is expected to conclude in December 2023. Target enrolment for the study is 90 participants. Protocol version: V2.0, 01092020.

## Data Availability

Data results from this randomized controlled study will be unavailable at the time of publication. Individual participant data will be available upon request.

## Abbreviations

ICU: Intensive care unit
EN: Enteral nutrition
PN: Parenteral nutrition
APACHE-II: Acute Physiology and Chronic Health Evaluation-II
GRV: Gastric residual volume
AE: Adverse event
ADR: Adverse drug reaction
DSMB: Data safety monitoring board
ELISA: Enzyme linked immunosorbent assay
